Cardiovascular disease is the leading cause of death and disability in China [17]. Large dietary surveys indicate that low levels of nuts consumption could be a significant contributor to CVD burden in China, with estimated mean nuts intake of only 5.4 g/day across diverse geographical regions [18]. An appropriately designed and powered RCT to test the effect of nuts supplementation on the risk of incident CVD events in China is therefore of significant scientific and public health importance. We hereby report the protocol for a 6-month walnut supplementation trial in a rural area of China with high rates of CVD, to obtain data on feasibility of long-term walnut supplementation to support and help to refine the design of a future long-term large RCT testing the effect of nuts supplementation on CVD risk. The main objectives of the current trial are to assess the acceptability and adherence to two different doses of walnut supplementation (30 and 60 g per day). The exploratory objectives are to determine the effects of walnut supplementation on cardiovascular risk factors including blood lipids, fasting glucose, and body weight.

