24-h dietary recall			╳				╳
Adherence and acceptability (intervention groups)					╳	╳	╳

^a^ 25 week or early withdrawal; ^b^ Weight, height, waist and hip circumference measurements

Interim visits occurred at 2 weeks and 3 months after the baseline for each participant. Blood test results describing blood lipids were provided to participants at the 2-week study visit, with referral to local physicians for management if blood lipid levels exceeded clinical guidelines. Participants in the intervention groups were reminded to consume walnuts every day and completed a 7-item follow-up questionnaire (Supplementary material) related to acceptability and adherence to the walnut supplementation at both interim visits. Participants in the control group did not answer this questionnaire, but received non-edible gifts at each interim visit. At the end of trial (6 months after randomization), all participants completed the same 24-h dietary recall as they did at baseline to assess the change in nuts intake, and fasting blood samples were collected according to the same procedure as at baseline. At the end of the trial, participants from intervention groups again answered the 7-item questionnaire regarding the acceptability and adherence to walnut supplement, and the control group received a non-edible gift (Table 1). All the participants will be notified of the study results once the trial has been completed.

Any condition which required hospitalization was collected at each follow-up visit as adverse event. All adverse events were listed and reported to the ethics committees periodically. Participants who developed food allergy with hypersensitivity to any of the components of walnut in the intervention groups were referred to and had the allergy confirmed by a doctor. Intervention was discontinued among those participants but they were followed up until the end of the trial.

Study personnels were divided into an intervention delivery group (who were not blinded to the allocation of treatment) and an outcome assessment group (who were blinded to the allocation of treatment). The intervention delivery group delivered the walnuts and non-edible gifts and performed the interim study visit questionnaires related to acceptability and adherence. The outcome assessors administered the FFQ, anthropometric assessments, and 24-h dietary recall and collected blood samples from participants at baseline and at the end of trial.

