### Study outcomes

The primary outcome for the study was fasting plasma alpha-linolenic acid (ALA), which was measured at baseline and 6 months. Walnuts are one of the few dietary sources rich in ALA [30]. Prior studies have demonstrated that increased walnut intake leads to increased plasma ALA, suggesting that measurement of plasma ALA can be used as an objective biomarker to measure adherence to walnut supplementation [10, 31, 32]. Plasma ALA will be assessed using gas chromatography following previously published methods [33–35]. For quality control, identification, precision, and accuracy will be evaluated continuously with model mixtures of known fatty acid methyl esters and an in-house control pool, with identification confirmed by gas chromatography using a flame ionization detector. Based on prior experience, we expect high accuracy and precision for the measurement of ALA (with inter-assay coefficient of variation to be < 10%). Secondary outcomes included participants’ self-reported walnuts intake, adherence and acceptability of the supplement walnuts, as assessed by the 24-h diet recall and 7-item questionnaire. Exploratory outcomes included body weight, plasma lipids (total cholesterol, LDL-C, HDL-C, total triglycerides), and fasting blood glucose.

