### Statistical analysis

Differences in between group post-treatment mean plasma ALA will be assessed by linear regression. In the primary analyses, study group assignment will be treated in the ANCOVA model as a categorical independent variable, with the control as the reference group. There will be three pair-wise comparisons: 1) 30 g/day walnut group vs. control, 2) 60 g/day walnut group vs. control, 3) 60 g/day walnut group vs. 30 g/day walnut group. Analyses will adjust for baseline plasma ALA and villages, and follow the intention-to-treat principle. An additional sensitivity analysis will be performed stratified by the baseline CVD status to examine any potential effect modification on the primary outcome.

For the secondary outcome of self-reported mean walnut intake (g/day) assessed by 24-h diet recalls, and the exploratory outcomes (plasma CVD lipids risk factors), differences in end of trial mean values between groups will be assessed by linear regression following the same approach as for the primary outcome.

Self-reported consumption patterns and satisfaction related to walnut intake will be assessed by the 7-item short questionnaire. The questionnaire included the following items: whether the participants consumed the walnuts, the ways they consumed the walnuts, and the number of times of walnuts intake in a day (each will be summarized as frequencies and %); as well as the number of days per week the participants consumed walnuts and their satisfaction rating on walnut flavour (will be summarized as mean ± SD).

Statistical significance is defined as two tailed α = 0.05.

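### Hospital admission is the only stated adverse event criterion, so walnut hypersensitivity without admission is not said to be listed or reported, and no described item gives a cause for reduced intake.

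*Protocol article*

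**What the plan says.** Under Data collection and follow up, the article sets the adverse event rule in one sentence: "Any condition which required hospitalization was collected at each follow-up visit as adverse event". The next sentence gives the reporting route: "All adverse events were listed and reported to the ethics committees periodically". No other kind of event is called an adverse event.

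The paragraph then turns to allergy: "Participants who developed food allergy with hypersensitivity to any of the components of walnut in the intervention groups were referred to" a doctor, who confirmed the diagnosis. The consequence follows: "Intervention was discontinued among those participants but they were followed up until the end of the trial".

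The Background section gives the trial's purpose: "The main objectives of the current trial are to assess the acceptability and adherence to two different doses of walnut supplementation". Study outcomes lists as secondary "adherence and acceptability of the supplement walnuts, as assessed by the 24-h diet recall and 7-item questionnaire". The Statistical analysis section describes the questionnaire items in two groups: "whether the participants consumed the walnuts, the ways they consumed the walnuts, and the number of times of walnuts intake in a day", and "the number of days per week the participants consumed walnuts and their satisfaction rating on walnut flavour". The questionnaire goes to the two walnut groups at 2 weeks, 3 months and 6 months; controls do not answer it. Its full text is in supplementary material that is not at hand.

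**The concern.** Admission to hospital usually marks an event as serious. Here it is the threshold for counting an event at all. A confirmed hypersensitivity reaction that ends the intervention is a harm of the intervention, yet if the participant is not admitted it falls outside the rule that precedes it in the same paragraph. A trial that follows the text exactly could send the ethics committees a list with no walnut-related event while participants had stopped because of reactions.

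The second consequence concerns the dose question. The section on the rationale for the walnut intervention asks whether the higher dose is as acceptable as the lower one. If intake is lower at 60 g, the designers of the planned trial of more than 20,000 people need to know whether taste, forgetting or intolerance was the cause. Nothing described in the article separates these.

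**Working it through.** The article gives no figure for harms, so there is none to reproduce. Its power calculation for plasma ALA has no bearing on this point. The check is a comparison of texts, followed by an illustration.

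**1. Adverse event rule against allergy route (Data collection and follow up)**

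| Case | Meets the stated criterion? | Said to be listed and reported? | Otherwise identified? |
|---|---|---|---|
| Any condition, admitted | Yes | Yes | – |
| Confirmed walnut hypersensitivity, admitted | Yes | Yes | Yes: referral, confirmation, discontinuation, follow-up |
| Confirmed walnut hypersensitivity, not admitted | No | No | Yes, by the same route |
| Gut or other symptom, not admitted | No | No | No route described |

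The third row is the internal inconsistency. The fourth is a gap in what is described.

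**2. Can the described instruments show intolerance?**

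- Questionnaire: five items are described (whether walnuts were eaten, how, times per day, days per week, flavour rating). None asks about symptoms or reasons. 7 − 5 = 2 items are not described.
- 24-h dietary recall at baseline and 6 months: shows amount eaten, not cause.
- Plasma ALA at baseline and 6 months: shows exposure, not cause.

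Lower intake at 60 g than at 30 g would thus be visible. Its cause would not be, unless one of the two undescribed items asks for it. Because controls do not answer the questionnaire, it could not supply a background symptom rate even then.

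**3. Illustration of size**

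Inputs: n = 70 per arm (Sample size section), or 70 × (1 − 0.10) = 63 after the 10% drop-out allowed there. The true rate p of a reaction without admission is an assumption; the article gives none.

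Probability of at least one case in an arm = 1 − (1 − p)^n:

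| Assumed p | n = 70 | n = 63 |
|---|---|---|
| 1% | 1 − 0.99^70 = 50.5% | 46.9% |
| 2% | 1 − 0.98^70 = 75.7% | 72.0% |
| 5% | 1 − 0.95^70 = 97.2% | 96.1% |
| 10% | 1 − 0.90^70 = 99.9% | 99.9% |

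Under the stated criterion the number of such cases classed as adverse events is zero in every row. The table shows only that an arm of this size would usually reveal a common reaction if it were asked about. It does not show that reactions are common.

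**The case against.** Three stronger readings are tempting, and the document supports none of them.

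- *Walnut allergy goes unrecorded.* It does not. The article gives allergy its own route, with continued follow-up, so cases are found by design. What is absent is the link from that route to the adverse event list. It is also fair to say that the adverse event sentence does not expressly exclude other events; it simply states no other criterion.
- *Tolerability of the two doses cannot be judged.* This goes too far. Tolerability is not a named outcome. Stopping or cutting down would show in the questionnaire at three visits, in the 24-h recall and in plasma ALA. Only the cause is out of reach.
- *Gut symptoms are captured nowhere.* This cannot be asserted. Two questionnaire items are not described, and the full protocol, which may define adverse events more fully, is not shown.

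The other side can add that the exclusions (nut allergy, fat intolerance, people who never or rarely eat nuts) lower the expected reaction rate, and that a hospitalisation threshold with a separate allergy route may be proportionate for a commercially available food. Both are reasonable, and the first is why the 5% row should not be taken as a forecast. Neither removes the inconsistency. The article did not leave the criterion to another document; it stated one, and its own foreseen harm can fall outside it.

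**Conclusion.** The point holds in limited form. The stated criterion leaves doctor-confirmed hypersensitivity without admission unclassified as an adverse event and not said to reach the ethics committees. On the items described, a dose difference in intake could be observed but not attributed to intolerance.

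The first conclusion rests on the article's text alone. The second is conditional on the two undescribed items not asking for symptoms or reasons. The size is not computable from the document; the probabilities of about 50%, 76% and 97% at assumed rates of 1%, 2% and 5% are illustrative. The primary analysis of plasma ALA is not affected. The change is worth making because it is cheap and bears on both harms reporting and the choice of dose for the larger trial.

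**What to change.** Reconcile the adverse event and allergy sentences under Data collection and follow up. Record confirmed hypersensitivity, and any symptom leading to reduced or stopped walnut intake, as an adverse event whether or not the participant was admitted; list these by arm and include them in the reports to the ethics committees. Unless the full questionnaire already does so, ask one identical symptom question in all three arms at the existing visits, so that the control group supplies a background rate.

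The article describes the visits in the past tense. If follow-up is complete, report allergy discontinuations by arm from the existing records, state the limit on harms ascertainment, and use the wider definition in the planned large trial.

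The cost is a wording change, one question that also has to be put to controls, and more events to list. The added symptom data would be self-reported by participants who know their allocation, so differences between walnut and control arms need cautious reading. No new visits or procedures are required.

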### Study outcomes

The primary outcome for the study was fasting plasma alpha-linolenic acid (ALA), which was measured at baseline and 6 months. Walnuts are one of the few dietary sources rich in ALA [30]. Prior studies have demonstrated that increased walnut intake leads to increased plasma ALA, suggesting that measurement of plasma ALA can be used as an objective biomarker to measure adherence to walnut supplementation [10, 31, 32]. Plasma ALA will be assessed using gas chromatography following previously published methods [33–35]. For quality control, identification, precision, and accuracy will be evaluated continuously with model mixtures of known fatty acid methyl esters and an in-house control pool, with identification confirmed by gas chromatography using a flame ionization detector. Based on prior experience, we expect high accuracy and precision for the measurement of ALA (with inter-assay coefficient of variation to be < 10%). Secondary outcomes included participants’ self-reported walnuts intake, adherence and acceptability of the supplement walnuts, as assessed by the 24-h diet recall and 7-item questionnaire. Exploratory outcomes included body weight, plasma lipids (total cholesterol, LDL-C, HDL-C, total triglycerides), and fasting blood glucose.

### Sample size

The sample size of 210 individuals (70 in each arm) provided more than 90% power with two-sided alpha of 0.05 to detect a mean difference of 0.12% (as percent of total fatty acid) in plasma ALA between the 30 g walnut supplementation and control arms [10]. The power estimation assumed a standard deviation (SD) of 0.18 and allowed for a drop-out rate of 10%. The study had similar power to detect a mean difference of 0.12% in plasma ALA comparing the 60 g/day and 30 g/day walnut supplementation groups. The power estimations were conservative since the assumptions were based on the PREDIMED trial that provided lower doses of walnuts (15 g/day) than the doses employed in this trial [10].

### Statistical analysis

Differences in between group post-treatment mean plasma ALA will be assessed by linear regression. In the primary analyses, study group assignment will be treated in the ANCOVA model as a categorical independent variable, with the control as the reference group. There will be three pair-wise comparisons: 1) 30 g/day walnut group vs. control, 2) 60 g/day walnut group vs. control, 3) 60 g/day walnut group vs. 30 g/day walnut group. Analyses will adjust for baseline plasma ALA and villages, and follow the intention-to-treat principle. An additional sensitivity analysis will be performed stratified by the baseline CVD status to examine any potential effect modification on the primary outcome.

For the secondary outcome of self-reported mean walnut intake (g/day) assessed by 24-h diet recalls, and the exploratory outcomes (plasma CVD lipids risk factors), differences in end of trial mean values between groups will be assessed by linear regression following the same approach as for the primary outcome.

Self-reported consumption patterns and satisfaction related to walnut intake will be assessed by the 7-item short questionnaire. The questionnaire included the following items: whether the participants consumed the walnuts, the ways they consumed the walnuts, and the number of times of walnuts intake in a day (each will be summarized as frequencies and %); as well as the number of days per week the participants consumed walnuts and their satisfaction rating on walnut flavour (will be summarized as mean ± SD).

Statistical significance is defined as two tailed α = 0.05.

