### Rationale for the chosen walnut intervention

Walnuts contain a high amount of protein, dietary fibre, vitamins, minerals and phytosterols [24]. Walnuts are a rich source of both omega-6 and omega-3 polyunsaturated fatty acids (linoleic and alpha linolenic acid [ALA]) [25] and improve cardio-metabolic risk factors in short-term clinical feeding trials including lowering LDL-cholesterol [26, 27]. Walnuts have made up the largest proportion (50%) of the mixed nuts used in the PREDIMED study [10]. In addition, walnuts are relatively soft compared to other nut types, making them easier to be chewed and consumed by those with oral health issues such as older adults, who are likely to make up a significant proportion of those recruited to the trial. Walnuts are also readily accessible since China grows a large volume of walnuts [28]. Commercially-available roasted, unsalted walnuts were used in the trial for enhanced taste and longer shelf life. The study walnuts contained 4.47 g of protein, 17.64 g of total fat, 5.73 g of carbohydrate and total energy of 811KJ per 30 g.

A dose-response relationship between greater nuts intake and lower cardio-metabolic risk has been generally observed across a range of nuts intake between 5 g to 100 g per day, with stronger effects for trials providing ≥60 g/day [1, 2]. Since the effect of walnut intake on CVD risk is likely mediated by changes in cardio-metabolic risk factors, we seek to evaluate if a higher dose of daily walnut supplementation is as acceptable as a lower dose. Therefore, for this trial, we tested both 30 g per day (corresponding to many current dietary recommendations), as well as a higher dose of 60 g per day of walnut supplementation.

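### The article asks whether 60 g/day is as acceptable as 30 g/day, but its only between-dose tests are of mean ALA and total grams, which do not address that question

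*Protocol article*

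**What the plan says.** The Background sets the aim: "The main objectives of the current trial are to assess the acceptability and adherence to two different doses of walnut supplementation". The section on the rationale for the walnut intervention adds a comparative question: "we seek to evaluate if a higher dose of daily walnut supplementation is as acceptable as a lower dose".

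The Statistical analysis section then fixes the following:

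- **Primary outcome:** "Differences in between group post-treatment mean plasma ALA will be assessed by linear regression", by ANCOVA adjusted for baseline ALA and village, with three pairwise contrasts, one of them 60 g versus 30 g.
- **Recalled walnut intake (g/day, 24-h recall):** the same regression and contrasts.
- **Questionnaire:** five items are named (whether walnuts were eaten, how, times per day, days per week, flavour rating). They are to be summarised as frequencies or as mean and SD. No between-dose comparison is stated.
- **Significance:** "Statistical significance is defined as two tailed α = 0.05".

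On size, the Sample size section says "The sample size of 210 individuals (70 in each arm) provided more than 90% power with two-sided alpha of 0.05". The target for 30 g versus control is an ALA difference of 0.12, and the same 0.12 is used for 60 g versus 30 g. The section calls this conservative because "the assumptions were based on the PREDIMED trial that provided lower doses of walnuts (15 g/day").

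**The concern.** Whether 60 g is as acceptable as 30 g is a question about how each arm does relative to what it was given. Mean ALA and mean grams measure how much was eaten in total. The 60 g arm is given twice as much, so it can eat a clearly smaller share of its allocation and still show the higher mean. A non-significant contrast does not help either, because failing to find a difference in ALA is not evidence of equal acceptability.

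The comparison with control has a milder form of the same problem. A difference from zero shows that the arm ate some walnuts. It does not show that the arm kept to its dose.

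The results are meant to inform a later trial anticipated at more than 20,000 participants. If the significant contrasts are reported without a direct dose comparison of adherence and acceptability, readers may credit them with an answer that they do not contain.

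**Working it through.** **Inputs (Sample size section).** 70 per arm; two-sided alpha 0.05; difference 0.12; SD 0.18; 10% drop-out, so 70 × 0.90 = 63 evaluable per arm.

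**The plan's own figure.** SE = 0.18 × √(2/63) = 0.0321. Power at 0.12 = Φ(0.12/0.0321 − 1.96) = Φ(1.78) = 96%. This agrees with the stated figure of more than 90%.

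**Dose contrast, by arithmetic alone.**

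- 65% of 60 g = 39 g; 90% of 30 g = 27 g. The arm with the lower adherence is ahead by 12 g.
- 45% of 60 g = 27 g. Adherence half as good as 90% of 30 g gives no expected difference in grams.

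So both a positive and a null contrast are compatible with worse adherence to 60 g.

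**Smallest significant ALA difference.** 1.96 × 0.0321 = 0.063.

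**Conversion to grams.** The article gives no ALA response per gram eaten, so two calibrations are assumed, both linear through zero:

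| | 0.12 per 15 g (0.008 per g) | 0.12 per 30 g (0.004 per g) |
|---|---|---|
| Significance threshold (about 50% power) | 7.9 g, 26% of 30 g | 15.7 g, 52% of 30 g |
| 80% power: (1.96 + 0.84) × 0.0321 = 0.090 | 11.2 g, 37% | 22.5 g, 75% |
| 90% power: (1.96 + 1.28) × 0.0321 = 0.104 | 13.0 g, 43% | 26.0 g, 87% |
| Power for the 12 g gap above | difference 0.096, about 85% | difference 0.048, about 32% |

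The first column follows the dose that the earlier trial provided. The second follows the article's own use of 0.12 for 30 g versus control and for the 30 g step between doses. If adjustment for baseline ALA reduces the residual SD (assumed correlation 0.3 to 0.7), the 26% threshold falls to 25% to 19%.

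**Precision of a direct comparison.** With an assumed 80% adherent in each arm, the 95% half-width for the difference is 1.96 × √(2 × 0.8 × 0.2/63) = 0.14. For non-inferiority on the same rates with 80% power, 63 per arm supports a margin of about 20 points; 15 points needs 112 per arm and 10 points needs 252.

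**The case against.** The strongest reply is that this is a feasibility trial, for which estimation is a legitimate choice. The article plans arm-level estimates that bear directly on adherence: recalled grams per day, the proportion eating the walnuts, times per day, days per week and flavour rating, with the questionnaire given at 2 weeks, 3 months and 6 months. This stands, and it rules out saying that the trial cannot answer its adherence question.

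A reader might also infer that p<0.05 on ALA is the criterion for adherence, or that the dose for the later trial will be chosen from that contrast. No section says so; the article says only that the results will support or inform the later design. Adherence cut-offs or margins may be in the full protocol or the SAP, which are not shown, so their absence from the article is no fault.

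The calibration is also open to objection. The earlier trial provided 15 g/day, which is not known to be what was eaten. It did so alongside other nuts and Mediterranean-diet advice. The gram conversions are therefore illustrations over a range.

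What the reply does not remove is the mismatch. The comparative question is stated, the between-dose tests are stated, and those tests are of something else.

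**Conclusion.** The point holds as a mismatch between a stated question and the stated tests. The listed 60 g versus 30 g contrasts address total intake; equal acceptability is not compared. This conclusion needs no dose-response assumption, since 39 g against 27 g is enough to show it.

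The related point on control holds with wider limits. Significance on ALA can be reached well short of full intake: at about 26% of the 30 g dose on the 15 g calibration, or about 52% on the 30 g calibration, both assuming linearity. It is tempting to say that the trial is positive with a quarter of the low dose eaten. That goes too far: 26% is the threshold, where power is only about one half, and 80–90% power needs about 37–43% of the dose even on the more favourable calibration. Likewise, the power of about 85% for the less adherent 60 g arm falls to about 32% on the other calibration.

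**What to change.** Keep ALA as the primary outcome with its three contrasts. In the Statistical analysis section:

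1. Add a 60 g versus 30 g comparison of the share of allocated dose consumed (24-h recall grams divided by allocated grams), days per week and satisfaction rating, adjusted for village, each reported as a difference with its 95% confidence interval.
2. State that p<0.05 on ALA alone does not establish adherence to a dose or equal acceptability of the two doses.
3. As a sensitivity analysis, count participants without a 6-month answer as non-adherent.

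A fixed non-inferiority margin is not advised: at an assumed 80% adherence this sample supports only about 20 points. Nor is a rule based on the fraction of an expected ALA response, which would rest on the untested calibration.

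The cost is wording and a few extra models on data already collected. The downsides are modest precision (about ±14 percentage points at 80% adherence) and reliance on a one-day self-report for the share of dose.

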## Methods

### Study design

The ‘Nuts for the prevention of cardiovascular disease in Chinese adults’ (NUTS) study was a randomized, controlled, single blind (blinded investigators and blinded assessments of all study endpoints), three-group parallel design trial lasting for 6 months.

Participants were randomized to one of the three groups in a 1:1:1 ratio: control (non-edible gift), low dose (30 g/day) walnut intervention group, and high dose (60 g/day) walnut intervention group (Fig. 1). Written informed consent was obtained from each study participant.

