### Intervention and control

Participants in the intervention groups were provided sachets containing 30 g of roasted and unsalted walnuts free of charge. For the 30 g/day arm, 1 sachet/day was provided, and for the 60 g/day arm, 2 sachets/day were provided. The walnuts were purchased from a local food manufacturer who sourced walnuts from Chinese walnut growers and packaged them in accordance with Chinese food standards (GB/T 20398–2006). The participants were instructed to open and consume the allocated dose of walnuts at any time of the day according to their personal preference, but not to share the walnuts with family members. To ensure freshness, participants were provided with sufficient sachets for the first 3 months of the intervention at baseline and were provided with the remainder at the 3-month follow-up study visit.

Participants in the control group continued with their usual diet without introduction of any nuts supplement. They were provided with small, inedible toiletry gifts at baseline and were provided with similar gifts at each follow-up visit to ensure equal study contacts across all the study groups and encourage attendance at the follow-up visits.

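### The ordinary three-arm ANCOVA for recalled walnut intake uses one residual variance where spread probably rises with dose, so its standard errors are likely somewhat wrong (minor)

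*Protocol article*

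**What the plan says.** The protocol article, under Statistical analysis, defines the primary model for plasma ALA: "study group assignment will be treated in the ANCOVA model as a categorical independent variable, with the control as the reference group". It adjusts for baseline ALA and village, and makes three pairwise comparisons (30 g vs control, 60 g vs control, 60 g vs 30 g) at two-sided 0.05. For recalled walnut intake in g/day it then says that "differences in end of trial mean values between groups will be assessed by linear regression following the same approach as for the primary outcome".

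Neither sentence names a standard-error estimator. The words pooled variance do not appear, and no robust or unequal-variance option is mentioned.

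The section Intervention and control fixes what each arm can eat from study supply: "For the 30 g/day arm, 1 sachet/day was provided, and for the 60 g/day arm, 2 sachets/day were provided". For the third arm, "Participants in the control group continued with their usual diet without introduction of any nuts supplement".

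**The concern.** A linear model fitted to three arms in the usual way estimates one residual variance and uses it for every contrast. That suits an outcome with similar spread in each arm. Intake handed out in fixed sachets is unlikely to behave so. If the same fraction of people take their allocation on the recall day, the SD produced by taking or not taking it is twice as large at 60 g as at 30 g.

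Equal arm sizes protect a two-group comparison against unequal variances. They do not protect here, because a variance averaged over three arms is applied to contrasts that involve only two.

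What is at stake is the precision reported for the secondary adherence outcome, mainly for 60 g vs 30 g. The section on the rationale for the intervention says the two doses are there to see whether the higher one is as acceptable as the lower.

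**Working it through.** **The plan's own figure.** The Sample size section says the "sample size of 210 individuals (70 in each arm) provided more than 90% power with two-sided alpha of 0.05", for an ALA difference of 0.12 with SD 0.18 and 10% drop-out. That leaves 70 × 0.9 = 63 per arm. The noncentrality is (0.12/0.18) × √(63/2) = 3.74, and Φ(3.74 − 1.96) = 96.3%. The claim of more than 90% is reproduced, and nothing below alters it.

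**Inputs for the recall outcome.** From the protocol: three equal arms, 63 evaluable per arm, doses of 0, 30 and 60 g in 30 g sachets. Assumed, because the protocol gives none: the arm SDs s0, s30 and s60.

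**Why spread should rise with dose.** If a fraction p takes the full allocation on the recall day, the SD is dose × √(p(1 − p)). At p = 0.8 this is 30 × 0.4 = 12 g and 60 × 0.4 = 24 g.

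**Formula.** Covariates aside, with n per arm:
- model variance of any contrast: 2 × (s0² + s30² + s60²)/3 ÷ n
- true variance for arms a and b: (sa² + sb²) ÷ n
- r = √(model variance ÷ true variance); coverage of a nominal 95% interval = 2Φ(1.96r) − 1

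For 60 g vs 30 g the interval is too narrow whenever 2·s0² < s30² + s60². Control variance only has to lie below the average of the two walnut arms; it need not be near zero.

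**One case in full, SDs 5/10/20 g.** Variances are 25, 100 and 400, with mean 175, so the model numerator is 350 for every contrast. The true numerators are 125, 425 and 500. Thus r = √(350/125) = 1.67, √(350/425) = 0.91 and √(350/500) = 0.84.

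| Assumed SDs (control/30 g/60 g) | 30 g vs control: r, coverage | 60 g vs control: r, coverage | 60 g vs 30 g: r, coverage |
|---|---|---|---|
| 5/10/20 | 1.67, 99.9% | 0.91, 92.5% | 0.84, 89.9% |
| 11.5/12/24 (control not near zero) | 1.43, 99.5% | 0.90, 92.1% | 0.89, 91.8% |
| 10/12/14 (mild) | 1.10, 96.8% | 1.00, 94.9% | 0.93, 93.1% |
| 12/12/12 | 1.00, 95% | 1.00, 95% | 1.00, 95% |

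**Check by simulation.** Sachet-based intake, 63 per arm, adjustment for baseline and six villages, 4000 runs for each of six assumed adherence patterns. Coverage with ordinary standard errors was 98.6–99.9% (30 g vs control), 92.3–93.6% (60 g vs control) and 88.8–91.8% (60 g vs 30 g). With HC3 it was 93.8–96.5% throughout. At 80% adherence in both walnut arms, the ordinary SE was 3.02 g for every contrast, against true SEs of 1.91, 3.32 and 3.68 g.

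**Effect on tests.** Every simulated contrast had a mean difference of at least 18 g. The smallest ratio of difference to true SE was 18/4.36 = 4.1, so significance would hardly change.

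The exception is equal mean intake in the two walnut arms. Suppose 80% take 30 g and 40% take 60 g, so both average 24 g, and 5% of controls eat 20 g. The variances are 20² × 0.05 × 0.95 = 19, 30² × 0.8 × 0.2 = 144 and 60² × 0.4 × 0.6 = 864. The model numerator is 2 × 1027/3 = 684.7, against a true 144 + 864 = 1008, so r = 0.82. The 60 g vs 30 g test then rejects 2 × (1 − Φ(1.96 × 0.824)) = 10.6% of the time at nominal 5%. Simulation of this pattern gave 10.4% with ordinary and 5.3% with HC3 standard errors.

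**The case against.** The strongest reply is that the protocol does not state the error. Linear regression with HC3 standard errors is still linear regression, and the choice of variance estimator is often left to a statistical analysis plan, which is not shown here. This stands in part: a common residual variance is the default reading of ANCOVA, not the protocol's wording. But the protocol does commit this outcome to the ALA approach without qualification, and followed in its ordinary form that is the weaker method for sachet-driven intake.

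Second, every magnitude rests on assumed SDs. This stands. A reader might infer from the usual-diet control that control intake is close to zero. The protocol gives no such figure: it excludes people who never or rarely eat nuts, and its 5.4 g/day is a national mean for all nuts. The Discussion does call sustained daily walnut intake in controls unlikely. The point does not need near-zero intake, as the 11.5/12/24 row shows.

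Third, the contrast is secondary; plasma ALA is the primary measure of adherence, and no rule ties the choice of dose to the recall comparison. This stands and limits the severity.

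**Conclusion.** The point holds as a minor one, confined to the recalled-intake outcome. If spread rises with dose and the default standard error is used, the interval for 30 g vs control is too wide, that for 60 g vs 30 g too narrow, and that for 60 g vs control slightly too narrow. For 60 g vs 30 g, coverage of a nominal 95% interval is about 90% under a strong dose gradient in SD, 93% under a mild one, and correct with equal SDs. Point estimates are unaffected, and the contrasts with control would remain significant.

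Two stronger readings are not supported. A reader might infer that the false-positive rate for 60 g vs 30 g is generally doubled; it approaches 10% only if lower adherence at 60 g makes the two mean intakes about equal. A reader might also infer that the primary ALA analysis is compromised. Adding assumed adherence variation to the SD of 0.18 lowers 60 g vs 30 g coverage only to 92.6–93.4%, and that SD may already contain such variation.

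**What to change.** Keep the linear model, its covariates and its point estimates. State that all three contrasts of recalled walnut intake use HC3 standard errors or, equivalently in purpose, arm-specific residual variances. This takes one sentence in the analysis plan and one software option. Sample size and primary power do not change, and the loss of efficiency if the variances prove equal is negligible. Doing the same for plasma ALA is optional.
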